Thus, this paper describes the rationale, design, and methodologies used in a factorial randomised controlled trial (Cardiometabolic HIIT-RT Study), wherein we hypothesised that HIIT and combined training would result in greater improvements in vascular function compared to RT and usual clinical care.

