## Methods/design

### Study design and setting

The present study is a RCT (ClinicalTrials.gov ID: NCT02715063). The Cardiometabolic HIIT-RT Study is a single-blind, randomised controlled, 2 × 2 factorial trial. The study received ethical approval from the Medical Research Ethics Committee of The University of Manuela Beltran (ID 06-1006-2014). Random allocation to treatment will be performed at the individual level.

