### Data collection and outcome measures

Outcome measures will be assessed at baseline and at 12-week follow-up by personnel blinded to the treatment allocation. Data will be recorded on standardised forms and entered into a secured-access database that contains quality control checks (e.g. range checks, notification of missing data).

The primary outcome measure is endothelial function as measured by flow-mediated dilatation (FMD). The secondary outcome variables include HR variability, pulse wave velocity (PWV), weight, BMI, WC, body composition, body temperature, biochemical profile, health-related physical fitness, self-perceived health, health-related quality of life (HRQL), and side effects. Other variables of interest include 24-hour dietary recall, lifestyle and demographic characteristics (Table 3 and Figure 3).

**Table 3 Tab3:** Summary of time point measurements of the primary and secondary outcomes of the study

Type of outcomes	Specific outcomes	Measurements		
		1-baseline (week 0)	2-moment (week 4)	3-moment (week 12)
Primary outcomes	Endothelial function as measured by flow-mediated vasodilatation	X		X
Secondary outcomes	Vascular function: heart rate variability, aortic pulse wave velocity, augmentation index and blood pressure	X		X
	Morphological component: weight, height, BMI, waist circumference	X	X	
	Body composition: fat mass and non-bone lean body mass	X		X
	Body temperature	X		X
	Plasma samples and biochemical analysis: LDL cholesterol (LDL-c), HDL cholesterol (HDL-c), total cholesterol, triglycerides, glucose, glycated haemoglobin (HbA1c)	X		X
	Fitness component: self-reported fitness, 1RM, hand-grip and peak uptake of volume of oxygen	X		X
	Self-perceived health: health-related quality of life	X		X
	Recent Physical Activity Questionnaire	X	X	X
	Demographic information	X		
	Side effects	X	X	X

*1RM* one repetition maximum, *BMI* body mass index

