### Power calculation and sample size

The aim of this study is to obtain data on the effects of HIIT, RT or combined training that will result in similar improvements in cardiometabolic health compared to the usual clinical care group. The measurement of FMD, validated in several population studies, was selected as the critical variable to calculate the sample size [59, 60]. To calculate the required sample size, we will use the formula for the comparison of two means:$$ n={\left[A+B\right]}^2\times 2\times S{D}^2/DIF{F}^2, $$ where *n* = the sample size required in each group, *SD* = standard deviation of the outcome variable, and *DIFF* = size of desired difference between groups. *A* and *B* depend on the desired significance level and desired power, respectively. Using estimates obtained from the literature [59, 60] and our previously performed study [61, 62], a sample size of 12 subjects in each group will be needed to reach a power of 80 % to detect a difference in means in the FMD of 2 % in the FMD after 12 weeks of training, assuming a SD of 2.7 using a two-sample *t* test with a 0.05 two-sided significance level. Assuming a drop-out rate of 15 %, the total minimal sample size has been increased to 15 subjects for each group. We believe that this sample size is feasible and realistic based on our previous experiences in RCTs [33, 34, 59, 60, 63, 64].

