#### Statistical analyses

The final data will be analysed using IBM SPSS 22.0 (SPSS, Inc., Chicago, IL, USA) and SAS software (SAS Institute Inc., Cary, NC, USA). An exploratory analysis will be performed to determine the frequency, range, variability, and distribution type for each variable to use the most appropriate statistical test when comparisons will be necessary. These analyses permit the assessment of the primary analysis of the data and will be undertaken using the principle of intention-to-treat (ITT). The ITT analysis for this study will include all participants, including those who are not fully compliant and those with missing outcome data. Because this is an experimental design with two measures of the primary and secondary outcomes, the first at baseline x0 (t0 = weeks) and the second after interventions x1 (t1 = 12 weeks) in four study groups, a comparative analysis between these measures to establish differences will be executed. To perform these comparisons, one-way ANOVA or Kruskal-Wallis tests will be applied when appropriate. Subsequently, a multivariate analysis will be carried out, and the autocorrelation between repeated measures will be taken into account. We will use longitudinal analysis methods, such as a generalised estimating equation approach, to control the differences among measures at baseline and to incorporate incomplete observations into this analysis. Finally, we will investigate if there is an interaction between the two interventions for the primary outcome at 12 weeks of supervised training HIIT, RT or combined training (HIIT + RT). For these analyses, we will include appropriate interaction terms in the models [38, 65]. The trial is not powered to detect these interactions and is likely to have poor precision for the interaction terms. We plan to report regression coefficients for the interaction terms and their 95 % confidence intervals. However, we aim to recruit 15 participants per group (a total of 60) to accommodate for a 20 % attrition rate and elimination due to non-compliance.

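### No single analysis is fixed for FMD, and the only named between-group test, a four-group omnibus test, does not isolate the hypothesised HIIT effect of the 2 × 2 factorial

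*Protocol article*

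**What the plan says.** The design statement reads "The Cardiometabolic HIIT-RT Study is a single-blind, randomised controlled, 2 × 2 factorial trial". The Background gives a directional hypothesis: "we hypothesised that HIIT and combined training would result in greater improvements in vascular function compared to RT and usual clinical care". The primary outcome is FMD (Data collection and outcome measures).

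The Statistical analyses section then sets out a sequence:

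1. An exploratory look at each variable, including the "distribution type for each variable to use the most appropriate statistical test when comparisons will be necessary".
2. A comparison of the four study groups: "To perform these comparisons, one-way ANOVA or Kruskal-Wallis tests will be applied when appropriate".
3. A multivariate stage using longitudinal methods, "such as a generalised estimating equation approach, to control the differences among measures at baseline and to incorporate incomplete observations into this analysis".
4. An investigation of the interaction between the two interventions on the primary outcome, reported with coefficients and 95 % confidence intervals. The section concedes that the trial is not powered for it.

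No sentence says which step is confirmatory for FMD. The Power calculation and sample size section words the aim differently, as concerning "HIIT, RT or combined training that will result in similar improvements in cardiometabolic health compared to the usual clinical care group", and sizes the trial on a two-sample t test.

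**The concern.** A factorial trial earns its efficiency by using every participant to estimate each main effect. The Background hypothesis is that kind of question: two HIIT-containing arms against two arms without HIIT. A one-way test over four groups spends 3 degrees of freedom on any difference among the arms. A significant result would not say that HIIT works, because an effect of RT alone could produce it. A non-significant result could hide a real HIIT effect that the targeted contrast would have detected. The only factorial quantity the section plans is the interaction, for which it expects poor precision.

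Because nothing fixes which of the listed analyses counts, the FMD conclusion could rest on any of them after the data are seen. The two statements of the aim make it harder still to tell which question the main test should answer.

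**Working it through.** **Inputs.** Difference of 2 FMD percentage points, SD 2.7, two-sided 0.05, 12 per group before dropout and 15 recruited (Power calculation and sample size). Four cells (Study design and setting). The correlation between baseline and week-12 FMD is not given; I assume r from 0.3 to 0.7.

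**The plan's own figure.** The printed formula gives n = (1.960 + 0.842)² × 2 × 2.7² / 2² = 28.6, so 29 per group, not 12. A two-sample t test between two arms has power 0.41 at 12 per arm and 0.50 at 15. That is a separate problem. It matters here because the pooled contrast is how 60 participants can approach the intended 80 %.

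**Omnibus test, means 0/2/0/2** (usual care/HIIT/RT/combined). Noncentral F on 3 and 4n − 4 df, with λ = n × Σ(μ − mean μ)² / SD² and Σ = 4.
- n = 12: λ = 48 / 7.29 = 6.58, power 0.52.
- n = 15: λ = 60 / 7.29 = 8.23, power 0.63.

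By symmetry, means 0/0/2/2 (RT effective, HIIT not) give the same λ and the same power, so a significant omnibus result cannot tell the two situations apart.

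**HIIT contrast**, mean of (HIIT, combined) minus mean of (RT, usual care). SE = √(4 × SD²/n × 1/4) = SD/√n, noncentral t on 4n − 4 df.
- n = 12: SE = 0.779, noncentrality 2 / 0.779 = 2.57, power 0.71.
- n = 15: SE = 0.697, noncentrality 2.87, power 0.80.

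**Baseline-adjusted**, replacing SD by SD × √(1 − r²) and using one further df:

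| r (assumed) | contrast, 12 per arm | contrast, 15 per arm | omnibus, 12 | omnibus, 15 |
|---|---|---|---|---|
| 0.3 | 0.75 | 0.84 | 0.56 | 0.68 |
| 0.5 | 0.83 | 0.90 | 0.66 | 0.77 |
| 0.7 | 0.94 | 0.98 | 0.83 | 0.92 |

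The adjusted omnibus columns (one df not deducted) show that part of the gain comes from baseline adjustment and part from asking the right 1-df question.

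**A pattern against the contrast, 0/2/2/2** (RT as good as HIIT, nothing added by combining). Σ = 3, and the pooled HIIT effect is (2 + 2)/2 − (0 + 2)/2 = 1.
- n = 12: λ = 36 / 7.29 = 4.94, omnibus 0.40; contrast noncentrality 1 / 0.779 = 1.28, power 0.24.
- n = 15: λ = 45 / 7.29 = 6.17, omnibus 0.50; contrast noncentrality 1.43, power 0.29.

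**Type I error** (simulation under the null, 6,000 runs per setting, 12 or 15 per arm, r = 0.3, 0.6 and 0.83): ANOVA 0.045–0.052; Kruskal-Wallis 0.045–0.049; choosing between them by a normality pre-test 0.047–0.054; GEE with uncorrected robust variance 0.09–0.11 for a 3-df Wald test and 0.06–0.07 for the HIIT contrast.

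**The case against.** **The statistical analysis plan may settle this.** Detail of that kind can be left to it. But the article does commit to tests, and the between-group test it names does not match the hypothesis it states. That mismatch stands whatever another document adds.

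**The power comparison uses a pattern that favours the contrast.** This stands as a downside. Under 0/2/2/2 the ranking reverses, and the interaction estimate would give limited warning: its SE is 2 × 2.7/√n, or 1.56 at 12 per arm, so an unadjusted 95 % interval extends about 3.1 either side of a true interaction of −2. But 0/2/2/2 departs from the Background hypothesis, which has RT doing worse than HIIT, so it does not defeat the choice of contrast.

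**The aim in the sample-size section can be read another way:** the three programmes improve outcomes similarly to one another, relative to usual care. A four-group test has some relevance to that, and the Discussion also asks which programme is better. This too stands, and is why the two statements of the aim need reconciling.

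**Stronger readings that the text does not support:**
- A reader might infer that the ANOVA is the declared primary analysis. It is not so labelled; the defect is that nothing is.
- A reader might infer that the plan ignores baseline FMD and incomplete cases. The longitudinal step is there expressly to handle both. The baseline criticism reaches the ANOVA step only.
- A reader might infer that choosing between ANOVA and Kruskal-Wallis after seeing the distributions inflates type I error. In simulation that choice holds about 5 %.
- A reader might assume six pairwise tests to follow. None are planned.
- A reader might take GEE inflation as built in. It arises only with an uncorrected robust variance, which the text does not specify, and GEE is named only as an example of the method.

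**Conclusion.** The point holds in this form: the Statistical analyses section lists several analyses without fixing which decides the FMD result, the only named between-group test does not isolate the Background hypothesis, and no HIIT main-effect test is named. Under that hypothesis (0/2/0/2, SD 2.7) the omnibus test gives up about 19 points of power at 12 per arm and 17 at 15 relative to the HIIT contrast.

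The size rests on no RT effect and no interaction. The 15-per-arm figures also need all 60 participants analysed, whereas the protocol allows for 15 % or 20 % loss in different sections. Reaching 80 % with 12 completers per arm depends on the assumed baseline correlation: 75 % at r = 0.3, 83 % at r = 0.5. Error-rate inflation is not part of the conclusion; it is a risk only if GEE is run without a small-sample correction.

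**What to change.** Name one primary analysis. Suggested wording: 12-week FMD % in a linear model with HIIT (yes/no), RT (yes/no), their interaction and baseline FMD; the primary test is the mean of (HIIT, combined) minus the mean of (RT, usual care), two-sided 0.05, with a model-based t interval. State the contrast explicitly, because with 0/1 coding and an interaction in the model the HIIT coefficient alone compares HIIT with usual care.

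To keep participants who have only a baseline value, fit it as a REML mixed model for baseline and week 12 with Kenward-Roger degrees of freedom; baseline FMD is then the first response rather than a covariate. If GEE is kept, specify a small-sample correction.

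Make ANOVA/Kruskal-Wallis secondary. Report the interaction with its 95 % CI beside the main effect, and say openly that the pooled contrast is the weaker test if RT works as well as HIIT with no additive gain. Reconcile the aim in the sample-size section with the Background hypothesis.

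The cost is protocol and analysis-plan wording, settled before outcome data are seen. It needs no extra participants, measurements or software.

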Overall, we will monitor each subject’s HR (FS1, Polar Electro Öy, Kempele, Finland) during the exercise sessions. We will estimate the energy expenditure during the exercise sessions by calibrating the energy expenditure to the HR during the VO_2_max tests performed at the baseline and post-intervention time points. The regression of the energy expenditure will be calculated for each participant according to HR and minutes spent exercising during the training sessions. Trainers will be physical therapists and physical educators with experience developing and monitoring exercise programmes among clinical populations. All protocol training will be performed under observation and supervision in an exercise laboratory with complete and strict monitoring of the amount of exercise completed in each session. Adherence to the exercise programme will be encouraged by the exercise professional who supervises each of the group sessions. To maximise adherence to the training programme each session will have a maximum of three to five participants training simultaneously. Attendance at supervised sessions includes compliance with target HR and expenditure energy and will be monitored and recorded by research staff. Each participant will meet with the study dietician for nutrition assessment and counselling, and an individualised nutrition intervention plan will be developed from the baseline food intake assessment according to participant preferences [35]. This plan is a standardised meal consisting of 1300 to 1500 kcal (50–55 % carbohydrates, 30–35 % total fat, less than 7 % saturated fat and 15–22 % protein).

At the beginning of the training protocol, we will obtain the participants’ weight to determine weekly energy expenditure necessary to achieve their target of 12 kcal kg^-1^ week^-1^ (iso-energetic). It is expected that the gradual increase in total energy expenditure will minimise fatigue, soreness, injuries, and attrition.

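### The plan keeps non-compliers in the intention-to-treat analysis, yet sizes recruitment to allow for eliminating them

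*Protocol article*

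**What the plan says.** All of the conflicting text is in the Statistical analyses section of the protocol article. On the analysis population it says: "The ITT analysis for this study will include all participants, including those who are not fully compliant and those with missing outcome data". The section closes with the recruitment target of 15 per group, 60 in total, and gives its purpose as "to accommodate for a 20 % attrition rate and elimination due to non-compliance".

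The Power calculation and sample size section reaches the same 15 by another route. It first says that "a sample size of 12 subjects in each group will be needed", and then: "Assuming a drop-out rate of 15 %, the total minimal sample size has been increased to 15 subjects for each group".

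On compliance itself, the Intervention section says: "Attendance at supervised sessions includes compliance with target HR and expenditure energy and will be monitored and recorded by research staff". The usual care group has no such sessions. It is asked to keep its activity level unchanged for the 12 weeks, and every participant is also to receive an individual nutrition plan. The article gives no threshold for non-compliance and names no per-protocol or other secondary population.

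**The concern.** A participant who does not comply cannot be both kept in the primary analysis and eliminated for not complying. The clause is also tied to the numbers. An allowance in the recruitment target is needed only for people who will be absent from the analysed set, so counting elimination in that allowance implies that those people are not analysed.

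What is at stake is the protection given by randomisation. Removing participants for behaviour after allocation leaves groups that are no longer comparable by design. The compliance that is recorded belongs to exercise sessions, so removal would probably be heavier in the three exercise arms than in usual care. Those removed would plausibly be people who gained little or who had a worse outlook. The remaining contrast with usual care would then tend to favour training while still being reported as ITT. With 15 per arm, three people make up 20 % of an arm, so a few decisions could matter.

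**Working it through.** **1. The plan's own figure.** Inputs: 12 per group needed and 15 % drop-out (Power calculation and sample size); 20 % attrition (Statistical analyses). The formula is n / (1 − loss).

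- At 15 %: 12 / 0.85 = 14.1, rounded up to 15.
- At 20 %: 12 / 0.80 = 15 exactly.

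The step from 12 to 15 therefore reproduces with attrition alone. The 12 is taken as given here. It does not follow from the stated inputs, since the article's formula with a difference of 2, an SD of 2.7, two-sided 0.05 and 80 % power gives 28.6, so 29 per group. That is a separate point, as is the disagreement between 15 % and 20 %.

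**2. Room for elimination.** At 20 % attrition, 15 × 0.80 = 12 remain, which leaves nothing for further loss. Elimination on top of that, at assumed rates, would leave in an exercise arm:

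- 10 % eliminated: 12 × 0.90 = 10.8
- 20 % eliminated: 12 × 0.80 = 9.6

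If instead the 20 % covers both kinds of loss and 15 % of it is drop-out, 5 % is left for elimination. The text does not say which is meant, so elimination rates of 5 % to 20 % are used below.

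**3. Illustration with a training effect.** Assumptions, none from the documents: compliers gain 2 FMD points (the article's target difference), non-compliers gain 0, and the two have the same prognosis. With a fraction e eliminated, the ITT effect is (1 − e) × 2 + e × 0, and the effect after elimination is 2.0.

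| e | ITT effect | After elimination | Overstatement |
|---|---|---|---|
| 5 % | 0.95 × 2 = 1.9 | 2.0 | 2.0 / 1.9, about 5 % |
| 20 % | 0.80 × 2 = 1.6 | 2.0 | 2.0 / 1.6, 25 % |

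**4. Illustration with no training effect.** Assume that non-compliers have an FMD lower by g standard deviations for reasons unrelated to treatment, that SD = 2.7 (from the article), and that elimination occurs only in the exercise arm. Let x be the mean of those retained, relative to the whole arm. Then (1 − e)x + e(x − 2.7g) = 0, so x = e × g × 2.7.

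- e = 20 %, g = 0.5: 0.20 × 0.5 × 2.7 = 0.27 points
- e = 20 %, g = 1: 0.20 × 1 × 2.7 = 0.54 points, which is 27 % of the 2-point target
- e = 5 %, g = 1: 0.05 × 1 × 2.7 = 0.135 points

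These are spurious differences before any adjustment for baseline FMD.

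**The case against.** The strongest reply is that the express rule governs. The article states plainly that non-compliers are analysed and adds a longitudinal method to use incomplete observations. The disputed words are only a purpose clause in a sentence about recruitment. They could refer to withdrawal from training or to a secondary analysis set out in the fuller protocol or the operations manual, which are not shown.

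Much of this stands. A reader might infer that participants will be eliminated from the primary analysis, only from the exercise arms, and that the result will therefore be biased. The documents do not support that:

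- No exclusion rule is stated, and the ITT rule may be the one followed.
- One-sided removal is inferred from what is recorded at sessions; the article does not define the non-compliance that would lead to elimination. Usual care has an activity requirement, and all participants have a nutrition plan, so someone in usual care who takes up exercise or ignores the diet could also be called non-compliant. In the comparison of HIIT or combined training with resistance training, both sides have sessions.
- The 25 % overstatement assigns the whole 20 % to elimination. The 0.54 points also requires a full 1 SD deficit. A lasting deficit would show in the baseline FMD too, so the planned baseline control would remove part of it.

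What does not stand is that the ITT sentence settles the matter. The contradictory clause justifies the number recruited, and no other population is named for it. Table 3 schedules FMD only at baseline and week 12. If elimination meant leaving follow-up, those people would have no outcome after baseline, and a standard unweighted generalised estimating equation relies on data missing completely at random, which is doubtful when non-compliance is the cause.

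**Conclusion.** The contradiction is real and concerns who is in the primary analysis. Confidence is high on the text and lower on the consequences. If elimination were carried out, it would be a post-randomisation exclusion, probably heavier in the exercise arms, and it could bias the contrast with usual care, probably towards training. Its size cannot be computed from the documents. Under the assumed values above, the reported effect would be 2.0 against an ITT effect of 1.9 to 1.6 with 5 % to 20 % eliminated. With no training effect, 20 % elimination would create a spurious 0.27 to 0.54 points for deficits of 0.5 to 1 SD, before baseline adjustment. The point should be corrected before analysis, because the present wording would allow an analysis that excludes non-compliers to be presented as ITT.

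**What to change.** Delete the reference to elimination for non-compliance from the last sentence of Statistical analyses, so that attrition alone justifies the target. State that no randomised participant is removed from follow-up or from the primary analysis for non-compliance, and that the week-12 FMD is sought from everyone, including those who stop training. If a compliance-based analysis is wanted, define its population and threshold in advance and report it only as a labelled secondary analysis.

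The cost is a few sentences and some effort to bring non-compliers to a visit that is already scheduled. The estimated effect may be smaller than it would be with non-compliers left out. The 15 per group is unaffected by this change, and no training or clinical rule is touched.
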